
### Preterm infants timing of assessments

All preterm infants will be asked to return to hospital for assessment at term equivalent age (39 to 42 weeks post menstrual age (PMA)), then further assessments at 12 and 24 months corrected age either at home or at the hospital (Table 1).

**Table 1 Tab1:** Outcome measures for preterm infants

Measures for Preterm infants	Baseline	Term Equivalent Age	12mth corrected	24mth corrected
Clinical	Demographics HNNE GMA	HNNE GMA NVS		Bayley-III
Infant Observation	IO	IO	IO	IO
Questionnaires	DASS MIBS EPDS	DASS MIBS EPDS	MIRI MPAS	DASS ITSEA MSES
Radiological		MRI		
Electrophysiological		dEEG		

HNNE = Hammersmith Neonatal Neurological Examination; GMA = General Movements Assessment; NVS = Neonatal Vision Scale; Bayley-III = Bayley Scales of Infant and Toddler Development, 3^rd^ Ed; IO = Infant Observation; DASS = Depression, Anxiety, Stress Scale; MIBS = Mother to Infant Bonding Scale; EPDS = Edinburgh Postnatal Depression Scale; MIRI = Maternal Infant Responsiveness Instrument; MPAS = Maternal Postnatal Attachment Scale; ITSEA = Infant Toddler Social and Emotional Assessment; MSES = Maternal Self Efficacy Scale; MRI = Magnetic Resonance Imaging; dEEG = dense array electroencephalography

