### Electroencephalography to assess function

Electrophysiological studies have reported significant differences in spectral electroencephalography (EEG) measures between healthy term and preterm infants [64–66]. Maturation of the EEG in preterm infants is characterised by decreases in the total amplitude and delta activity power in quiet and active sleep [67]. A preliminary study examining whether preterm infant massage has a beneficial effect on cerebral function as measured by EEG, found a significant difference in the interburst interval duration and also a difference in maturation of visual function in preterm infants who received massage in comparison to preterm infants who received standard care [68]. A subsequent study showed a relative increase in global EEG spectral power in delta and beta frequencies in massaged infants when compared to controls, which was interpreted as suggesting that massage therapy in low-risk preterm infants favors a process of maturation of brain electrical activity similar to that observed in term born infants [24].

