### Outcome measures

#### Primary outcome

The primary outcome measure is beta-frequency global power (EEG parameter) in preterm infants, at term equivalent age, who have received massage therapy or care as usual.

High-density electroencephalography (dEEG) will be recorded using a 64-electrode sensor net (HydroCel Geodesic Sensor Net, Electrical Geodesics Inc.). Each electrode is a saline sponge, in a geodesic tension structure comprised of silastic threads. The sensor net is prepared by soaking in a normal saline solution and then applied directly onto the head without need for further scalp preparation. The infant will be fed, wrapped and placed in an open cot, in a darkened room fitted with a Faraday cage. The recording will be conducted during sleep. EEG signals are amplified by a GES 300 series amplifier (Electrical Geodesics Inc.), digitised (at a sampling rate of 256 Hz) and recorded to the hard drive of a Mac desktop computer via NetStation software (Electrical Geodesics Inc.). The EEG data files will be exported from NetStation software then pre-processed and analysed quantitatively using Curry Scan 7 Neuroimaging Suite signal processing software (Compumedics Neuroscan™, Compumedics Limited, Australia).

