
### Healthy term born infants

Once written informed consent has been obtained, an appointment will be arranged for the infants to undertake the same assessments as the preterm cohort, at term equivalent age (39 to 42 weeks postmenstrual age) and infant observations at 12 months of age (Table 2).

**Table 2 Tab2:** Outcome measures for term born infants

Measures for Term born infants	42 weeks post menstrual age	12 months corrected
Clinical	HNNE GMA NVS	
Infant Observation	IO	IO
Questionnaires	DASS MIBS EPDS	
Radiological	MRI	
Electrophysiological	dEEG	

HNNE = Hammersmith Neonatal Neurological Examination; GMA = General Movements Assessment; NVS = Neonatal Vision Scale; IO = Infant Observation; DASS = Depression, Anxiety, Stress Scale; MIBS = Mother to Infant Bonding Scale; EPDS = Edinburgh Postnatal Depression Scale; MRI = Magnetic Resonance Imaging; dEEG = dense array electroencephalography

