### Data analysis

Summary statistics will be used to describe demographic and clinical data characteristics at baseline by allocated study treatment. Continuous data will be summarised using either mean and standard deviation, or median and inter-quartile range, depending on the distribution of the variable of interest. Categorical data will be presented as frequencies and percentages. Comparisons between the baseline values of the treatment groups will be conducted to assess the degree to which variables are comparable after randomisation. Between group differences will be investigated using linear regression for continuous data and Fisher’s exact test for categorical data. Potential confounding variables for the primary outcome are considered a-priori to be: gestational age at birth, birthweight, parity and maternal education. If any of these variables differ significantly between-groups (at *P* < 0.005), the identified variable(s) will be controlled for in the main analyses.

The primary study outcome is beta frequency global power measured in all VPT infants at term equivalent age. The mean difference between treatment groups will be calculated using linear regression with treatment group entered as the main effect. The corresponding 95 % Wald confidence interval and *p*-value will be reported. For secondary outcomes, we will present the effect estimate relating to a variable with a continuous outcome as a mean difference, which will be calculated using a linear regression model. If a continuous variable does not meet the assumptions necessary for linear regression, we will compare groups using the Mann–Whitney U Test. We will present the effect estimate relating to a variable with a binary outcome as an odds ratio, which will be calculated using a logistic regression model. We will present the effect estimate relating to a variable with a count outcome as an incident rate ratio, which will be calculated using a Poisson regression model. For all models the corresponding 95 % Wald confidence interval and p-value will be reported.

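### The primary EEG may be recorded anywhere from 39 to 42 weeks, but the stated model cannot adjust for postmenstrual age at recording; separately, the term reference visit is 39 to 42 weeks in the text and 42 weeks in Table 2

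*Protocol article*

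**What the plan says.** All of this is in the protocol article.

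- **Visit window.** Under Preterm infants timing of assessments, preterm infants return at "term equivalent age (39 to 42 weeks post menstrual age (PMA"). Table 1 places the dense-array EEG at that visit.
- **Primary outcome.** Under Primary outcome: "The primary outcome measure is beta-frequency global power (EEG parameter) in preterm infants, at term equivalent age".
- **Primary model.** Under Data analysis, the group difference comes from "linear regression with treatment group entered as the main effect".
- **Covariates.** The same section names the candidate confounders for the primary outcome in advance: "gestational age at birth, birthweight, parity and maternal education". The entry rule begins "If any of these variables differ significantly between-groups" and sets the threshold at P < 0.005. PMA at recording is not on the list.
- **Maturation.** The Background section on electroencephalography states: "Maturation of the EEG in preterm infants is characterised by decreases in the total amplitude and delta activity power". It also reports that the pilot's relative increase in delta and beta power was read as maturation towards term-born activity.
- **Term reference group.** The text under Healthy term born infants schedules the same assessments "at term equivalent age (39 to 42 weeks postmenstrual age"). Table 2, in the same section, heads that column as 42 weeks PMA.

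**The concern.** The trial treats its EEG outcome as a marker of brain maturation, yet infants may be recorded up to three weeks apart in age. Gestational age at birth does not stand in for age at recording: two infants born at the same gestation can be recorded at opposite ends of the window.

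This is not a detail left to a later analysis plan. The article states the primary model and a closed list of variables that may enter it, so even a visible PMA imbalance would not bring PMA in. At stake is precision in a trial planned on 20 completers per arm.

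The term group exists to show what a normal infant looks like at the same age. If its visit is scheduled differently from the preterm visit, age is mixed with the effect of prematurity in that comparison.

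**Working it through.** **Inputs from the article.** Window of 39 to 42 weeks, so 3 weeks wide. Sample size section: 10% difference in EEG power, type 1 error 0.05, 80% power, 20 completers per group, two thirds retained, 60 recruited. Data analysis section: two-tailed tests.

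**Assumptions, because the article gives no figure.** Visits are spread uniformly over the window. The correlation between PMA at recording and beta power is r = 0.2 to 0.5.

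**1. The plan's own figures.** Attrition reproduces: 20 / (2/3) = 30 per group, 60 in total. The 20 cannot be reproduced forwards because no SD is stated, so I solved backwards. The standardised effect is (1.960 + 0.842) × √(2/20) = 0.886, which implies an SD of 10 / 0.886 = 11.3% of the mean. With the t distribution the figures are 0.909 and 11.0%.

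**2. Spread of age.** PMA SD = 3/√12 = 0.87 weeks. If 42 weeks is read as running to 42 weeks and 6 days, the width is 27/7 = 3.86 weeks and the SD is 1.11 weeks.

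**3. Chance imbalance with 20 per arm.** SE of the difference in mean PMA = 0.87 × √(2/20) = 0.27 weeks, a 95% range of about ±0.54 weeks. On the wider reading it is 0.35 and ±0.69 weeks. A PMA gap of 0.5 weeks moves the contrast by (r/0.866) × 0.5 × 11.3 percentage points.

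**4. Precision and power.** Adjustment multiplies the SE by √(1 − r²).
- Case A: the planning SD already contains the PMA spread. Adjusted power comes from the noncentral t with 37 df and noncentrality 0.909 × √(20/2) / √(1 − r²).
- Case B: the planning SD came from a narrower age range. The unadjusted effect shrinks to 0.886 × √(1 − r²) (normal approximation).

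| r | SE cut by adjusting | Case A: power, adjusted | Case B: power, unadjusted | Case B: n per arm needed unadjusted | Shift from a 0.5-week gap (points, against 10) |
|---|---|---|---|---|---|
| 0.2 | 2% | 82% | 78% | 21 | 1.3 |
| 0.3 | 5% | 84% | 76% | 22 | 2.0 |
| 0.4 | 8% | 86% | 73% | 24 | 2.6 |
| 0.5 | 13% | 90% | 68% | 27 | 3.3 |

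The shift column is not an extra loss. A chance imbalance is part of the sampling error that the unadjusted confidence interval already covers; the column shows what adjustment would remove in a given sample.

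**5. Term reference visit.** The text gives 39 to 42 weeks, as for the preterm infants. The Table 2 heading gives 42 weeks only. If the table were followed exactly and preterm visits were uniform (mean 40.5 weeks), the reference infants would be 42 − 40.5 = 1.5 weeks older on average.

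**The case against.** The strongest reply is that the randomised comparison is sound as written. Both arms share one window, EEG analysis is blinded, and an unadjusted linear regression is valid under randomisation. This stands. A reader might infer that leaving PMA out biases the primary result. That would require the arms to attend at different ages, and nothing in the article says they will. The section on Potential confounders speaks of control parents withdrawing, not of visit timing.

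It is also fair that the maturation statement concerns total amplitude and delta power, while the outcome is beta power. The pilot's beta finding is described in terms of maturation, but no slope per week is given. The correlations above are therefore assumptions, and at r = 0.2 the gain is only about two points of power. In Case A nothing is lost against plan, because the planned 80% already absorbs the scatter; adjustment is then a gain. Only in Case B does the trial fall short of plan. The article does not show which case applies.

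On the term group, a reader might infer a bias of 0.52 to 0.87 SD (r × 1.5 / 0.866 at r = 0.3 and 0.5) and conclude that the benchmark cannot be read. The article does not support this. It would need the table to override the text, every term infant to be seen at exactly 42 weeks, uniform preterm visits, and the assumed correlation. The heading may be a labelling slip, and the article does not settle which version was meant. Nor does the Data analysis section specify a term-versus-preterm test.

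What remains is that the model and covariate list are fixed without PMA at recording, and that the two term-visit statements disagree.

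**Conclusion.** The point holds as a matter of precision. The primary EEG may be recorded across three weeks of age, and the stated model and closed covariate list leave that scatter in the residual, with no way to adjust for a chance imbalance. The randomised contrast is not biased by this alone.

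The size is unknown. Assuming uniform visits, r = 0.2 to 0.5 and a planning SD that already includes the age spread, adjustment lifts power with 20 per arm from 80% to about 82 to 90%. If the planning SD excluded that spread, unadjusted power would be about 78 to 68%.

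The disagreement between the text and Table 2 is documented and separate. Following the table would make the reference infants older on average than the preterm infants, by an amount that the article does not fix. It affects only the comparison with the ten reference infants and lends no weight to the point about the primary model.

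**What to change.** 1. Pre-specify PMA at recording (in days, centred) as a covariate in the primary model, whatever the observed balance, and in the other regression models at term equivalent age for EEG, MRI, HNNE and NVS outcomes.
2. Report the distribution of PMA at assessment by arm.
3. Report the primary model without PMA as a sensitivity analysis, because PMA at the visit is measured after randomisation. If timing did differ by arm, the two models could diverge, and the reader should see both.
4. Reconcile the text and Table 2 for the term group so that reference infants are assessed in the same PMA window as the preterm infants.
5. Adjust any term-versus-preterm comparison for PMA. A shared window alone does not align the ages: reference infants are born at 37 to 41 weeks, and one born at 41 weeks cannot be seen at 39.

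PMA at each visit follows from gestational age at birth and the visit date, so no new data are needed. The cost is one residual degree of freedom (38 to 37 with 40 completers), one sensitivity analysis, and one reconciled visit description.

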### Outcome measures

#### Primary outcome

The primary outcome measure is beta-frequency global power (EEG parameter) in preterm infants, at term equivalent age, who have received massage therapy or care as usual.

High-density electroencephalography (dEEG) will be recorded using a 64-electrode sensor net (HydroCel Geodesic Sensor Net, Electrical Geodesics Inc.). Each electrode is a saline sponge, in a geodesic tension structure comprised of silastic threads. The sensor net is prepared by soaking in a normal saline solution and then applied directly onto the head without need for further scalp preparation. The infant will be fed, wrapped and placed in an open cot, in a darkened room fitted with a Faraday cage. The recording will be conducted during sleep. EEG signals are amplified by a GES 300 series amplifier (Electrical Geodesics Inc.), digitised (at a sampling rate of 256 Hz) and recorded to the hard drive of a Mac desktop computer via NetStation software (Electrical Geodesics Inc.). The EEG data files will be exported from NetStation software then pre-processed and analysed quantitatively using Curry Scan 7 Neuroimaging Suite signal processing software (Compumedics Neuroscan™, Compumedics Limited, Australia).

### Secondary outcomes

i.Other EEG parameters at term equivalent age (TEA)Global power in delta, theta and alpha bands, absolute and relative power for each frequency band, interhemispheric coherence and partial directed coherence will be analysed.ii.MRI measures at TEAA brain MRI will be performed using a 3.0-T (Siemens TIM Trio, Erlangen, Germany) and an MRI-compatible incubator with a dedicated head coil (LMT Lammers Medical Technology, Lubeck, Germany). The infants will be fed, fitted with earmuffs to minimise noise exposure (Natus Mini Muffs, Natus Medical Inc., San Carlos, CA) and monitored by pulse oximetry, then wrapped and placed in an MRI-compatible incubator to keep the infant still, warm and supported in the scanner. Scanning will occur for about 45 to 60 min without sedation.The MRI protocol will include T1 turbo spin echo (TSE), T1w MPRage, T2w HASTE and 3 echo T2 map, 30 direction diffusion weighted imaging (DWI), and 64 direction DWI sequences. A neuroradiologist will review clinical sequences and classify any white and grey matter [58, 97] abnormalities. Diffusion images will be acquired using single-shot echo planar multi-direction diffusion-weighted sequence, employing dual bipolar diffusion gradient and double spin echo. This will include the acquisition of a 30 direction DWI protocol (b = 1000s/mm^2^) and a 64 direction HARDI protocol (b = 2000s /mm^2^), in which the encoding gradients are uniformly distributed in space (acquisition time 5 min and 11 min respectively). A field map for diffusion data is acquired using two 2D gradient recalled echo images to assist in correction for residual distortions due to susceptibility in homogeneities (acquisition time 1 min). An extensive pre-processing and quality control procedure will be used to detect and correct image artefacts caused by head movement, cardiac pulsation, and image distortions [60]. Fractional anisotropy (FA) and mean diffusivity (MD) will be estimated from corrected diffusion data using a diffusion tensor model. Constrained spherical deconvolution implemented in MRtrix will be employed to estimate fibre orientation distribution (FOD) [98]. Whole-brain voxel based analysis of FA and MD will be performed using tract-based spatial statistics optimised for neonates [99]. Whole-brain voxel-based analysis of fibre orientation distributions will be conducted using Apparent Fibre Density (AFD) [100]. Probabilistic tractography will be performed using MRtrix. White matter pathways will be delineated using the multi-regions-of-interest approach. A number of pathways, including corticospinal tract, corpus callosum, superior longitudinal fasciculus and thalamic radiations will be extracted. Summary measures of FA, MD, AFD and T2 within pathways will be calculated and related to EEG and clinical findings.iii.Preterm infant clinical measures8.Clinical assessments performed at baseline will also be performed at TEA; Prechtl’s Qualitative General Movements Assessment (GMA) [45] and Hammersmith Neonatal Neurological Examination (HNNE) [92]. All examinations will be performed by a Paediatric Neurologist, Paediatric Physiotherapist or Neonatologist blinded to allocation groups.A visual assessment will be performed at TEA. The Neonatal Vision Scale (NVS) [47] is a clinical assessment consisting of a short test battery that explores various aspects of visual function, ranging from the ability to fix and follow a target, to more complex aspects of visual function, such as reaction to a colour target, discrimination of black and white stripes with increasing spatial frequency and attention at a distance [47].The Bayley Scales of Infant and Toddler Development, Third Edition (Bayley-III) will be performed [48] at 24 months corrected age. Children will be assessed in the 5 key developmental domains of cognition, language, social-emotional, motor and adaptive behavior [48].The Infant Toddler Social and Emotional Assessment (ITSEA) will be measured at 24 months corrected age. The ITSEA is a 136-item parent report questionnaire to assess social and emotional problems and competencies in 4 domains of behavior: behavioural dysregulation; externalising behavior problems; internalising behavior problems and competencies [87].iv.Maternal measuresInfant Observation [85] performed at baseline will be repeated at TEA, 12 months and 24 months corrected age. This will be performed by the Psychoanalytic Psychotherapist who is blinded to randomisation.Questionnaires performed at baseline will also be performed at TEA; Depression Anxiety Stress Scales [79], Edinburgh Postnatal Depression Scale [95] and Mother-to-infant Bonding Assessment [96]. Mothers will be asked to complete these assessments.At 12 months corrected age, maternal infant responsiveness and maternal postnatal attachment will be measured. The MIRI, a 22-item scale [82] will be performed. The MPAS which has 19 items, all scored on a 5-point scale, with 1 and 5 indicating low and high attachment respectively, will also be performed [101]. Mothers will be asked to complete this assessment.At 24 months corrected age, the Maternal Self Efficacy Scale (MSES) will be measured. The MSES is a 20-item measure of the mothers’ perceived self-competence of their maternal practice used at 12 months. The measure has good internal consistency (Cronbach’s **α** = 0.76-0.89) and is a good predictor of maternal competence, with strong concurrent validity with observation [102]. Mothers will be asked to complete this assessment.

### Healthy term born infants

Once written informed consent has been obtained, an appointment will be arranged for the infants to undertake the same assessments as the preterm cohort, at term equivalent age (39 to 42 weeks postmenstrual age) and infant observations at 12 months of age (Table 2).

**Table 2 Tab2:** Outcome measures for term born infants

Measures for Term born infants	42 weeks post menstrual age	12 months corrected
Clinical	HNNE GMA NVS	
Infant Observation	IO	IO
Questionnaires	DASS MIBS EPDS	
Radiological	MRI	
Electrophysiological	dEEG	

HNNE = Hammersmith Neonatal Neurological Examination; GMA = General Movements Assessment; NVS = Neonatal Vision Scale; IO = Infant Observation; DASS = Depression, Anxiety, Stress Scale; MIBS = Mother to Infant Bonding Scale; EPDS = Edinburgh Postnatal Depression Scale; MRI = Magnetic Resonance Imaging; dEEG = dense array electroencephalography

### Blinding

Clinical assessors will be blinded to the intervention allocation. Likewise MRI and EEG data analyses will be performed in a blinded fashion.

### Potential confounders

Limitations include the single blinded nature of the study and the risk of potential contamination between intervention and CAU groups. Parents whose infants are allocated to the control group may be more likely to withdraw from the study after randomisation, if they perceive there is limited benefit to them.

### Data analysis

Summary statistics will be used to describe demographic and clinical data characteristics at baseline by allocated study treatment. Continuous data will be summarised using either mean and standard deviation, or median and inter-quartile range, depending on the distribution of the variable of interest. Categorical data will be presented as frequencies and percentages. Comparisons between the baseline values of the treatment groups will be conducted to assess the degree to which variables are comparable after randomisation. Between group differences will be investigated using linear regression for continuous data and Fisher’s exact test for categorical data. Potential confounding variables for the primary outcome are considered a-priori to be: gestational age at birth, birthweight, parity and maternal education. If any of these variables differ significantly between-groups (at *P* < 0.005), the identified variable(s) will be controlled for in the main analyses.

The primary study outcome is beta frequency global power measured in all VPT infants at term equivalent age. The mean difference between treatment groups will be calculated using linear regression with treatment group entered as the main effect. The corresponding 95 % Wald confidence interval and *p*-value will be reported. For secondary outcomes, we will present the effect estimate relating to a variable with a continuous outcome as a mean difference, which will be calculated using a linear regression model. If a continuous variable does not meet the assumptions necessary for linear regression, we will compare groups using the Mann–Whitney U Test. We will present the effect estimate relating to a variable with a binary outcome as an odds ratio, which will be calculated using a logistic regression model. We will present the effect estimate relating to a variable with a count outcome as an incident rate ratio, which will be calculated using a Poisson regression model. For all models the corresponding 95 % Wald confidence interval and p-value will be reported.

All analyses will primarily be undertaken using the ‘intention-to-treat’ approach, where all evaluable data is analysed in the treatment group according to which the participant was allocated, regardless of treatment received. Additionally, ‘per protocol’ analyses will be conducted where there have been large deviations from the planned intervention; all individuals with evaluable outcome data will be analysed according to the treatment they received (no massage/received < 50 % of total possible massage/received at least 50 % of total possible massage). Any such analyses will be clearly labeled as such and cautiously interpreted as perhaps indicating the maximum theoretical potential of the intervention. Statistical significance will be defined as alpha = 0.05. All tests conducted will be two-tailed.

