### Sample size

Preliminary data from a pilot study, which described global spectral EEG power-associated brain maturation in massaged preterm infants, was used to calculate a sample size [24]. To find a 10 % between-group difference in EEG power in the treatment group [24], with type 1 error rate 0.05, and power of 80 %, we require 20 participants in each group to complete the study. Assuming that two thirds of participants will remain in the study at term equivalent age, we will require a total of 60 preterm infants to be recruited (i.e. 30 per group).

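### Covariates enter the primary model only through a baseline significance test at P < 0.005, so the plan forgoes precision and leaves sub-threshold imbalances uncorrected; a short fixed covariate set would be better

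*Protocol article*

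**What the plan says.** All quotes are from the Data analysis section of the protocol article unless another section is named.

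- **Candidate covariates:** "Potential confounding variables for the primary outcome are considered a-priori to be: gestational age at birth, birthweight, parity and maternal education".
- **Baseline test:** "Between group differences will be investigated using linear regression for continuous data and Fisher’s exact test for categorical data".
- **Entry rule:** "If any of these variables differ significantly between-groups (at *P* < 0.005), the identified variable(s) will be controlled for in the main analyses".
- **Default primary model:** "The mean difference between treatment groups will be calculated using linear regression with treatment group entered as the main effect". If no covariate passes the gate, treatment group is the only term.
- **Trial significance level:** "Statistical significance will be defined as alpha = 0.05", and "All tests conducted will be two-tailed". No reason is given for using 0.005 at the gate.
- **Size (Sample size section):** "we require 20 participants in each group to complete the study". This is inflated to 30 per group because one third are expected to be lost by term equivalent age.

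The Randomisation section stratifies by gender only. The article nowhere commits to adjusting for any covariate regardless of the baseline test.

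**The concern.** Under sound randomisation, any baseline difference between the arms is due to chance. A P-value for that difference therefore does not show whether the variable matters for the analysis. What matters is how strongly the variable predicts beta-frequency global power, and the rule takes no account of that. A strong predictor with a modest imbalance stays out, while a weak one with a large imbalance goes in.

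Two things are at stake:

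- **Precision.** Adjusting for a predictive covariate removes outcome variance whether or not the arms happen to be balanced. A trial planned on 20 completers per arm gives that up almost always under this rule.
- **Conditional bias.** When a fairly large imbalance falls short of the threshold, the estimate carries it uncorrected. Randomisation makes such imbalances uncommon at entry. However, the plan expects to lose a third of infants by the primary time point, and its section on potential confounders says control families may be more likely to withdraw. The infants analysed may be less balanced than those randomised.

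**Working it through.** **Inputs from the article:** 20 completers per arm, 30 randomised per arm, two-sided alpha 0.05, 80% power, four candidate covariates, gate at P < 0.005.

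**Assumptions:** the article gives no SD for EEG power and no correlation between any covariate and beta power. Variance explained (R²) of 10 to 30% and correlations of 0.3 to 0.5 are illustrative.

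**1. The plan's own figure.** 20 / (2/3) = 30 per arm, 60 in total. This matches. The 20 itself cannot be checked without an SD. By a t-test calculation, 20 per arm at 80% power corresponds to a standardised difference of 0.909. That value is back-calculated, not stated in the plan.

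**2. Imbalance needed to pass the gate (continuous covariate).** Required standardised difference = t(0.9975, 2n − 2) × √(2/n).

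| Infants per arm | t critical | Required imbalance |
|---|---|---|
| 20 | 2.980 | 2.980 × √(2/20) = 0.94 SD |
| 30 | 2.918 | 2.918 × √(2/30) = 0.75 SD |

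Both sizes are shown because the article does not say whether the test uses all randomised infants or completers. The figures do not apply to a covariate tested by Fisher's exact test.

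**3. How often the rule adjusts.** For four independent variables, 1 − 0.995⁴ = 0.0199, or 2.0%. A simulation with correlated gestational age and birthweight, and Fisher's test for two binary covariates, gave 1.1 to 1.7% (3,000 runs per setting). At a gate of 0.05 the figures would be 1 − 0.95⁴ = 18.5% if independent, and about 10 to 14% simulated.

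**4. Validity.** In the same simulation, type I error was between 4 and 5.5% under the protocol rule, with no adjustment, and with constant adjustment for gestational age. The unconditional error rate is not inflated.

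**5. Precision not gained (20 per arm).** Adjustment changes the standardised difference to 0.909 / √(1 − R²).

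| Assumed R² | Standardised difference | Power |
|---|---|---|
| 0 (unadjusted) | 0.909 | 80% |
| 10% | 0.958 | 84% |
| 20% | 1.016 | 88% |
| 30% | 1.087 | 92% |

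Using 36 or 35 residual degrees of freedom instead of 38 leaves these rounded values unchanged. The simulation used a slightly smaller effect of 0.886 (normal approximation). It gave 79% both under the rule and unadjusted. Always adjusting for gestational age gave 82% at a correlation of 0.3 and 87% at 0.5.

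**6. Conditional bias.** Bias in outcome SDs = correlation × imbalance.

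- At 0.3 SD imbalance: 0.3 × 0.3 = 0.09 to 0.5 × 0.3 = 0.15.
- At 0.7 SD imbalance: 0.3 × 0.7 = 0.21 to 0.5 × 0.7 = 0.35, or 0.21/0.909 = 23% to 0.35/0.909 = 38% of the back-calculated design effect. Simulated type I error, given that imbalance at 20 per arm, was 9 to 16%.

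Neither imbalance passes the gate at either sample size. By chance alone, 0.7 SD or more in a given covariate has probability of about 3% at 20 per arm (t = 0.7/√(2/20) = 2.21) and 0.9% at 30 per arm (t = 0.7/√(2/30) = 2.71).

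**The case against.** The strongest defence is that the primary comparison is randomised and valid without adjustment. The rule is set in advance, uses baseline data only, and so cannot be steered by the outcome; the EEG analysis is also blinded. The sample size makes no allowance for covariates, so the stated 80% is not reduced. A rule that fires in about 2% of trials hardly makes the model data-driven in practice. All of this stands, and it makes the point one of efficiency and good practice. It does not justify the gate, because it amounts to saying that the gate does almost nothing.

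A reader might infer more than the article supports:

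- **That the primary test is biased or its type I error inflated.** This holds only conditional on a sizeable imbalance, which chance seldom produces. Overall error is about 5%.
- **That even a one-week difference in gestational age would go unadjusted.** This depends on an SD the article does not give. A uniform spread over the eligible window (SD about 1.40 weeks) gives P = 0.030 at 20 per arm and 0.008 at 30, so no adjustment. At 30 per arm the gate would open if the SD were below about 1.33 weeks, and at 20 per arm below about 1.06.
- **That the four variables are known to predict beta power.** The article calls them potential confounders and gives no correlations.

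The 0.005 may also be a misprint for 0.05, the trial's general level. The article cannot settle this. Adjustment would then be less rare, but the choice of covariates would still rest on a baseline test, and more often in practice.

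**Conclusion.** The concern holds as a shortcoming in efficiency and good practice, not as a threat to the validity of the primary test. The gate selects covariates on the wrong criterion. As written, it leaves the primary model unadjusted in about 98% of trials or more under randomisation.

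The general cost is forgone power: about 4, 8 or 12 percentage points at an assumed R² of 10, 20 or 30%. If the covariates explain little, the gain is small. The second cost is conditional bias from an imbalance below roughly 0.75 to 0.94 SD. This is uncommon by chance, but selective loss could add to it and the gate would seldom catch it. The trigger sizes and the 2% ceiling follow from the article's own figures, with the ceiling taken for independent covariates. The power gains and bias sizes rest on the stated assumptions.

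**What to change.** Delete the baseline significance tests as a route into the model, together with the P < 0.005 threshold. Keep the descriptive baseline table.

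State that the primary linear model always contains treatment group, gender (the stratification factor) and gestational age at birth, with birthweight added if wanted, for example as a z-score for gestation so that it does not largely repeat gestational age. Give a short reason for keeping or dropping parity and maternal education. Report the unadjusted estimate as a sensitivity analysis. If any threshold is retained elsewhere, confirm whether 0.005 was intended.

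The change is to wording only. Gestational age and birthweight are already baseline items, and gender is recorded for stratification. It uses two or three of the 38 residual degrees of freedom with 20 completers per arm. If the covariates explained nothing, power would fall only from 80.0% to about 79.8%. The change should be made before unblinding.
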